## Abstract

**Background:**

Chronic Obstructive Pulmonary Disease (COPD) is a disease state characterized by airflow limitation that is not fully reversible and usually progressive. Current guidelines, among which the Dutch, have so far based their management strategy mainly on lung function impairment as measured by FEV_1_, while it is well known that FEV_1_ has a poor correlation with almost all features of COPD that matter to patients. Based on this discrepancy the GOLD 2011 update included symptoms and impact in their treatment algorithm proposal. Health status measures capture both symptoms and impact and could therefore be used as a standardized way to capture the information a doctor could otherwise only collect by careful history taking and recording. We hypothesize that a treatment algorithm that is based on a simple validated 10 item health status questionnaire, the Clinical COPD Questionnaire (CCQ), improves health status (as measured by SGRQ) and classical COPD outcomes like exacerbation frequency, patient satisfaction and health care utilization compared to usual care based on guidelines.

**Methods/Design:**

This hypothesis will be tested in a randomized controlled trial (RCT) following 330 patients for two years. During this period general practitioners will receive treatment advices every four months that are based on the patient’s health status (in half of the patients, intervention group) or on lung function (the remaining half of the patients, usual care group).

**Discussion:**

During the design process, the selection of outcomes and the development of the treatment algorithm were challenging. This is discussed in detail in the manuscript to facilitate researchers in designing future studies in this changing field of implementation research.

**Trial registration:**

Netherlands Trial Register, NTR2643

## Background

Chronic Obstructive Pulmonary Disease (COPD), a common preventable and treatable disease, is characterized by persistent airflow limitation that is usually progressive and associated with an enhanced chronic inflammatory response of the airways and the lungs to noxious particles or gases [1]. COPD has a considerable impact on health status [2]. Most guidelines, amongst which the 2003 Global initiative for Chronic Obstructive lung Diseases (GOLD) guidelines [3], and the Dutch GP guideline [4], have based severity categorization on lung function impairment, more specifically the FEV_1_. It is, however, well known that the FEV_1_ has a poor correlation with almost all patient reported outcomes in COPD and therefore the impact the disease has on the patient [5].

The GOLD strategy document update December 2011 [6] is the first update in which symptoms and exacerbations are included in patient assessment and severity grading. However a detailed management strategy is not included. As far as the authors know, there currently is no study in which the severity grading is tested via prospective algorithms. This may be one of the reasons that the GOLD update has not yet been incorporated in national guidelines.

Health status instruments have been developed specifically to assess disease severity, measure disease impact and to evaluate treatment. The use of validated health status instruments in daily clinical practice offers a wide range of opportunities. Information can be collected in a standardized manner prior to consultation. This may help decrease the known underestimation by clinicians of the impact of the disease and its treatment on the patients quality of life [7,8] and make it easier to review the patients condition over longer periods of time [9]. Studies have also shown that patient satisfaction is improved and patient opinions are more positive when quality of life questionnaires form part of routine practice [8,10]. High patient satisfaction is known to lead to superior compliance [11,12], to more promptly seeking medical care [13] and to retaining a higher amount of information [14]. One of the important prerequisites for using a questionnaire in routine clinical care, is its validation on individual patient level. Most questionnaires have solely been validated for the use in groups of patients. Validation on the individual level requires a different methodology. In the field of COPD this is currently only performed for the CCQ [15,16].

The 2003 GOLD guidelines, on which Dutch national guidelines are based, advocate a stepwise algorithm based on FEV_1_ level, differentiation is only recommended on the level of pharmacological treatment recommendations. All non-pharmacological recommendations are identical for all levels of severity, limiting individual differentiation. We propose that health status instruments provide the opportunity for individually tailored advices, focusing on functional status, mental status and symptoms. A form of tailoring that is, in a certain way, akin to the rising interest in pheno typing patients to target interventions more effectively [17].

Studies carried out in routine clinical practice show promising results regarding the feasibility of the use of health status instruments and their influence on the consultation, however until now these studies have not been able to show consistent benefits on outcomes for patients with COPD [18-20]. These ambiguous results might be due to differences in questionnaires used and in the way studies were performed. Studies that test the clinical effectiveness of health status instruments have used a large variety of tools, settings, and outcome parameters [18-26]. However none of these studies used a clear algorithm on how to interpret the outcome of health status measures nor did they feature clear advice regarding patient management.

The 2013 GOLD update includes both the COPD Assessment test (CAT) and the Clinical COPD Questionnaire (CCQ) as health status measurements [1]. One of the advantages of the CCQ over the CAT is its domains. This enables identification of the patients’ prime problem and thereby a focusing of the treatment on this problem. Also, the CCQ was rated to be more useful in primary care practice [27,28] and has been validated for use in individual patients [15].

We hypothesize that a treatment algorithm that is based on a simple validated measure of health status, the Clinical COPD Questionnaire (CCQ), improves health status (as measured on a separate scale) and secondary parameters like exacerbation frequency, patient satisfaction and health care utilization, when compared to usual care based on FEV_1_ level as per current GOLD guidelines.

The research questions addressed are:

1. Does a treatment algorithm that is based on CCQ measurements improve health status as measured by SGRQ over two years of use compared to usual care based on FEV_1_?

2. Does such a treatment algorithm improve other parameters of COPD care such as exacerbation frequency, mental health, health care utilization and direct medical costs compared to usual care based on FEV_1_?

This study combines the advantages of standardized health status measurement in routine clinical practice and of clear clinical treatment recommendations.

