#### Algorithm example

CCQ group: a high score on CCQ total score (>3, i.e. severely impaired) in combination with the highest score on the functional status domain leads to a pulmonary rehabilitation program advice, while a total CCQ score between 1 and 2 in combination with the highest score on the functional status domain leads to the provision of leaflets on healthy movement. A CCQ total score < 1 represents a very low burden of disease or good disease control, so no change in treatment advice is given. The final algorithm is displayed in Figure 2.

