#### Secondary outcomes

One of the secondary outcomes is the exacerbation frequency as indicated by medication use. This is one of the classical COPD outcomes, and exacerbations have a large impact on patients’ lives.

Other secondary outcome parameters are changes in CCQ score, 6 minute walking distance test, HADS, mMRC, lung function, and differences between the two groups in hospital admissions and mortality.

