#### Economical outcome variables

Health care utilization and other direct medical costs are recorded. Data include medication use and all visits to the general practice, hospital, and other health care professionals involved in the management of COPD.

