### Statistical analysis

The primary outcome measures is the change in SGRQ over time. The SGRQ results in a total score and 3 subscale scores: symptoms, activities and impact. The SGRQ change in scores over the treatment period of the control group will be compared to that of the experimental group. The scores will be tested for normality. In case of normality the difference will be univariately tested with a student T-test and multivariately with a linear regression model. In case of deviation from normality the variable will be transformed to normality via a Box-Cox transformation and thereafter analyzed via student T-test and linear regression models.The multivariate models will be corrected for the following confounders: educational level, age, gender, current smoking, and FEV_1_. The number of exacerbations will be reported as weighted exacerbations rates (total number of exacerbations divided by the total person-time of follow up per group) [43-45]. Statistical significance of weighted rate ratios will calculated using a Poisson regression model. The secondary research outcomes will be tested in a similar fashion as the primary research question. The primary analyses will be based on the intention-to-treat principle. As secondary analyses, a per protocol analysis will be performed to increase insight in the data.

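### The only stated rule that can reach direct medical costs (normality test, Box-Cox, t-test) would not compare mean costs, and could favour the arm with the equal or higher mean if cost distributions differ between arms

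*Protocol article*

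**What the plan says.** The Background makes costs part of the second research question, which covers "mental health, health care utilization and direct medical costs compared to usual care". The hypothesis in the same section counts utilization among "secondary parameters like exacerbation frequency, patient satisfaction and health care utilization".

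Under Economical outcome variables the article says "Health care utilization and other direct medical costs are recorded" and names the items to be collected. It gives no method of comparison there. The Secondary outcomes section does not list costs. After exacerbation frequency it continues: "Other secondary outcome parameters are changes in CCQ score, 6 minute walking distance test, HADS, mMRC, lung function", followed by hospital admissions and mortality.

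The Statistical analysis section sets the rule for the primary outcome. First, "The scores will be tested for normality". If they are normal, a t-test and a linear regression follow. If not, the rule reads: "In case of deviation from normality the variable will be transformed to normality via a Box-Cox transformation and thereafter analyzed via student T-test". The transformed variable is also put through a regression model. Exacerbations get a Poisson model. Everything else is handled by one sentence: "The secondary research outcomes will be tested in a similar fashion as the primary research question". No other analysis of costs appears.

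**The concern.** What a treatment strategy costs depends on the arithmetic mean cost per patient, because the mean times the number of patients is the total. Per-patient costs are typically right-skewed. They would then fail a normality test, and the fitted Box-Cox transformation would be close to a log. A t-test on that scale compares roughly geometric means, which is a different quantity.

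The two comparisons agree in direction when the cost distribution has the same log-scale shape in both arms, and can part company when it does not. A difference in shape is possible here. In the Algorithm example section, CCQ-guided advice ranges from no change at a low total score, through leaflets, to a high score that "leads to a pulmonary rehabilitation program advice, while a total CCQ score between 1 and 2" contrasts with the leaflet case. A few costly patients could raise the mean of an arm whose typical patient costs less.

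Two further defects do not depend on shape. The adjusted linear regression gives a coefficient on the transformed scale, not in money. Box-Cox also needs strictly positive values, so the rule cannot run as written if any patient has zero cost.

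**Working it through.** **Inputs.** From the Sample size calculation section: 150 per group and alpha 0.05, taken here as two-sided. The article gives no cost figure, so there is none to reproduce and every cost distribution below is an assumption. The 150 was sized for the SGRQ. It is used only as the number per arm.

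**Step 1: what the rule compares.** For log-normal costs with median m and log-SD s, the mean is m × exp(s²/2). With A the CCQ arm and B usual care:

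mean ratio = (m_A/m_B) × exp((s_A² − s_B²)/2).

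A log-scale t-test sees only m_A/m_B, with z ≈ ln(m_A/m_B) / √((s_A² + s_B²)/150). If s_A = s_B, the exponential factor is 1 and the direction is right.

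**Step 2: three log-normal cases, by formula and by simulation (2000 trials each).** Each trial applied a Shapiro-Wilk test, Box-Cox on pooled data if p < 0.05, then a t-test. The comparator was a Welch test on raw costs. Normality was rejected in every data set and the average fitted lambda was 0.00 to 0.02.

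- *Equal spread:* medians 800 and 1000, log-SD 1.0 in both. Mean ratio 0.80. z = −0.223/√(2/150) = −0.223/0.1155 = −1.93, so P(CCQ declared cheaper) ≈ Φ(1.93 − 1.96) ≈ 0.49. Simulated: cheaper 47.7%, dearer 0%. The direction is correct.
- *Equal means:* medians 800 and 1000, log-SD 1.2 and 1.0. Mean ratio 0.80 × exp(0.22) = 0.80 × 1.246 = 1.00. z = −0.223/√(2.44/150) = −0.223/0.1275 = −1.75, so P ≈ Φ(1.75 − 1.96) ≈ 0.42. Simulated: cheaper 39.2%, against 4.5% for Welch.
- *Equal medians:* 1000 in both, log-SD 1.2 and 1.0. Mean ratio 1.25 and z = 0. Simulated: the rule declares CCQ dearer in 2.7%, Welch in 20.6%.

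**Step 3: a lump cost in a few CCQ patients.** Usual care is log-normal with median 1000 and log-SD 0.8, so its mean is 1000 × exp(0.32) = 1377. The CCQ arm has the same log-SD and a lower median, and a random 10% of its patients incur a fixed extra cost. Its mean is median × 1.377 + 0.10 × extra. There were 1500 trials per row.

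| CCQ median | Extra in 10% | CCQ mean | Ratio | Cheaper, Box-Cox | Cheaper, Welch |
|---|---|---|---|---|---|
| 700 | 4130 | 964 + 413 = 1377 | 1.00 | 38.1% | 2.8% |
| 700 | 5000 | 964 + 500 = 1464 | 1.06 | 32.1% | 1.2% |
| 800 | 2750 | 1102 + 275 = 1377 | 1.00 | 9.9% | 2.1% |
| 900 | 1377 | 1239 + 138 = 1377 | 1.00 | 2.4% | 2.6% |

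The nominal rate in this direction is 2.5%. Repeat runs of the four rows gave about 35–38%, 29–32%, 9–11% and 2.4–2.9% under Box-Cox.

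**Step 4: near-null checks (equal true means).**

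- Identical arms: 3.3% (Welch 2.4%).
- Same lump frequency and medians in both arms: 3.1% (Welch 3.1%).
- Lump in 5% of usual care and 10% of CCQ patients, CCQ median 900: 4.9% (Welch 2.3%).

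The excess appears only when shapes differ, and grows with that difference.

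**The case against.** The strongest reply is that the article does not prescribe this analysis for costs. Costs have their own heading, the secondary list omits them, and the catch-all sentence most naturally refers to that list. The list also contains mortality, which cannot be Box-Cox transformed and t-tested, so the sentence cannot be meant literally for every outcome. On that reading no cost analysis is stated, and a condensed article may leave one to the full protocol or analysis plan.

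Part of this stands: the rule's reach to costs is an inference. A reader might take it that the article explicitly orders a Box-Cox test of costs, and it does not. But the catch-all is worded in terms of research questions, costs are named in the second of these, and exacerbations alone are given another model. No other rule is on offer for costs, so an analyst following the article would end up with this one.

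The second reply is that the size comes from chosen inputs. That stands fully. A reader might infer from the algorithm that cost shapes must differ by design. The article does not support this. Its Discussion says the two treatments are not markedly different and share the same elements. The advice levels are examples, GPs may deviate from the advice, and recorded costs include medication and all COPD-related visits in both arms. Nor does the article establish that every patient's cost is positive.

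**Conclusion.** The point holds as a minor one on a non-primary economic outcome. If costs are analysed under the only stated rule that can reach them, the test will not address mean cost and the adjusted estimate will not be in money. If any patient has zero cost, the transformation is undefined. This rests on reading research question 2 together with the catch-all sentence, and on costs being right-skewed.

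A misleading direction is possible but conditional. Under the assumed distributions, the rate of falsely declaring the CCQ arm cheaper runs from about the nominal 2.5% when shapes are similar to about 10–38% when they differ strongly. With equal log-scale spread the direction is preserved.

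A reader might go further and infer that a costlier CCQ strategy is likely to be reported as saving money. Rates of 54% to 82% can be produced with a CCQ mean 4% to 13% higher, but only by assuming log-SDs of 1.2 against 0.8, 1.3 against 1.0, or 1.4 against 1.0. Nothing in the document supports spreads that unequal. The primary SGRQ comparison is not touched by this point.

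**What to change.** In the Statistical analysis section, exempt direct medical costs from the normality-test, Box-Cox and t-test rule. State that arithmetic mean cost per patient will be compared between arms on the untransformed scale, with a non-parametric bootstrap 95% CI for the difference. If covariate adjustment is wanted, use a generalised linear model for the mean, for example log link, gamma variance and robust standard errors, and report predicted mean cost per arm.

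This takes a sentence or two and a standard bootstrap, with no new data or patients. The drawback is a possibly wider interval than on the transformed scale, which reflects the real uncertainty in mean cost.

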## Methods/Design

### Study design

The study will be a prospective randomized controlled trial with a follow-up duration of two year with two arms:

•intervention group with CCQ guided treatment proposals (CCQ group) and

•guideline group for whom treatment advice is based on FEV_1_ level according to Dutch National and GOLD guidelines (Usual Care, UC group).

The study flow-chart is represented in Figure 1. The study has been approved by the Medical Ethical Committee of the University Medical Center Groningen and is registered on the Dutch trial register (ISRCTN-register) with the identifier NTR2643.

**Figure 1 F1:**
[figure not shown]
MARCH study flow chart.

### Duration

Patients will be followed up for 2 years and during that period there will be 7 visits, including a baseline and a final visit (Figure 1).

### Selection and recruitment

Local general practitioners will be contacted to participate in the study. When a general practitioner agrees to participate, he/she is asked to review his/her patient database for possible participants. The resulting eligible patients are sent a patient information leaflet and an informed consent form by their general practitioner. They will be asked by letter to return the informed consent form to their general practitioner if they wish to participate in the study (opt-in method). The patients will then be invited for the baseline visit. The inclusion criteria are a doctor’s diagnosis of COPD, age 40 years or above, a smoking history of at least 10 pack-years and a post bronchodilator FEV_1_/ forced vital capacity (FVC) <0.70. Exclusion criteria are a myocardial infarction less than 3 months ago, inability to read and understand the Dutch language, history of asthma or allergic rhinitis, regular use of oxygen, unstable or life-threatening co-morbid condition (as judged by the investigator) and dementia.

This study will take place in general practices in the Northern part of the Netherlands. All measurements including spirometry will be performed by a trained research nurse and will take place in or near the GP practices when possible.

### Randomization and blinding strategy

After inclusion into the study the patients will be randomized to the intervention or usual care group using a computerized randomization on individual patient level. The study will be performed in a double-blind fashion, patients and doctors will be blinded as well as the technicians that perform the measurements. A separate researcher will collect the data, and feed them in to a PC for a computerized treatment advice based on pre-defined criteria as per protocol. This advice will be sent to the doctor. Since the doctor will only see the resulting treatment advices, and not the measurement results they are based on, and since the treatment advices are compliant with the same national guide lines in both groups, albeit organized in a different fashion, blinding is maintained.

### Intervention

The actual intervention is the provision of treatment advices to the general practitioner based on health status in the CCQ group and based on FEV1 in the UC group.

### Algorithm development

#### Algorithm objective

CCQ group: the primary objective during the developmental phase was that the algorithm should result in a strategy that would treat the patient’s prime problem, reflected by the most impaired CCQ domain and not treat the remaining CCQ domains. At the next visit, it is assessed whether the impairments in the specific domain had improved sufficiently, the domain that is most impaired at that moment will guide the next period of treatment. The treatment intensity is guided by the CCQ total score, i.e. the overall impairment in health status.

UC group: this algorithm resulted directly from the treatment steps in the Dutch general practitioners guidelines.

#### Algorithm content

CCQ group: all current standard treatments options in the current Dutch general practitioners guidelines [4] were reviewed ([name]) (pharmacological, stop-smoking, reactivation, counseling etc.) and rated on intensity of the treatment and expected possible effects of the treatment on each CCQ domain: symptoms, functional status or exercise capacity and mental state ([name], [name], [name]). Subsequently the interventions were ordered according to intensity of the treatment and resources needed, e.g. for functional status this resulted in the following ordering: physical activity advices, out-patient reactivation, and rehabilitation.

UC group: all treatment steps in the Dutch general practitioners guidelines were directly translated into the algorithms.

#### Algorithm tuning

CCQ group: The concept treatment algorithm was discussed during an 45 minute meeting with pulmonologists and residents (n~15 present) working at the University Medical Center Groningen and during an one hour Groningen Research Institute for Asthma and COPD (GRIAC) research meeting. This GRIAC meetings are attended by both clinical and basic scientists of the departments of allergology, lab allergology and pulmonary diseases, epidemiology, general practice, molecular pharmacology, pathology, paediatric pulmonology and paediatric allergy, pulmonology and respiratory insufficiency. The concept algorithm was slightly altered as a result of these two meetings.

UC group: no further discussion nor fine tuning took place.

